#### Routine monitoring and evaluation

PSWs and CSWs complete a monitoring and evaluation (M&E) form at each contact with participants (home visit, self-help group meeting, etc.). M&E forms are designed to be short (15 min to complete, or less) and collect basic process data on the service provided (e.g. location and duration of contact, who participated, what tools/topics were covered).

The supervisor will also carry out semi-structured observation of intervention delivery. Supervisors will be requested to observe at least one intervention activity each week, using a semi-structured observation form to record insights into the providers’ performance, fidelity to the intervention manual, and the engagement of the participants (which should take no more than 30 min). For quality assurance, a SUCCEED researcher will also attend one intervention activity each month and record their observations using the same guide. Over the course of the 4-month follow-up period of the pilot, SUCCEED researchers should plan to record observations on at least one of each of the following:Facility visit (recruitment and/or accompaniment of a participant to health services)Community Mental Health ForumSelf-help group meetingLivelihoods activity

Data from M&E forms and semi-structured observations will be aggregated along with research administrative data (e.g. participant drop-outs) in monthly reports prepared by the supervisor at the host organisation for the SUCCEED research team. The SUCCEED research team may carry out quality checks, if indicated, to ensure that monthly reports are complete and there are no obvious errors.

#### Endline

A WHOQOL-BREF self-assessment for participants with lived experience of psychosis is repeated at approximately 4 months after recruitment, following the same procedures described above (see “Baseline”).

An endline ENACT competency assessment is also completed for SUCCEED providers (PSWs, CSWs) using an adapted version of the ENACT tool applied by a trained SUCCEED research worker and supervisor to assess trainee competencies (see “Provider competency”, above). The assessors will record their ENACT scoring for each provider on a paper-based form during a standardised role-play (estimated to last 15–20 min) [54]. The mean score between the two assessors will be calculated for each item and summed to provide an overall score (though we do not assign any a priori cut-off to determine competence level).

Endline qualitative data collection comprises interview and focus group discussions following semi-structured discussion guides tailored to each participant type. Interviews will take approximately 1 h, and each focus group will take approximately 2 h to complete. Both interviews and focus group discussions will have a trained facilitator and note-taker present and will be audio-recorded and transcribed, with permission. Facilitators will also be instructed to take notes immediately after each interview or focus group to jot down key points that surprised them, were in contradiction to the way in which they think about the topic at hand or affirmed a particular viewpoint, to contribute to the subsequent data analysis.

### Data management

Hard copies of data collection tools and notes will be kept in locked cabinets, and soft copies (i.e. audio recordings and transcripts) will be kept on secured, password-protected laptops that can only be accessed by SUCCEED researchers. All research equipment, hard and soft copies of data will be kept in locked offices. At least one researcher per SUCCEED study site has been nominated as a data manager and undergone additional training in data management provided by an experienced statistician [55]. All recordings will be destroyed once transcription has been completed and checked. With the exception of shared data deposited in repository,^2^ all research data will be destroyed 10 years after the completion of SUCCEED’s programme of research (April 2036), in line with LSHTM guidelines, unless local regulations stipulate otherwise.

Quantitative data will be collected using predesigned paper-based data collection tools and anonymised before entry. Data will be double-entered into a customised electronic data collection form with pre-programmed data checks. Further checks of range, consistency and completeness will be carried out, and data queries will be raised to clean the data. The data will be hosted on an LSHTM server and protected using asymmetric encryption keys. A codebook will list all variables and value labels along with a description and details on the tool and question from which they were derived.

Key informant interviews and focus group discussions will be captured via audio recordings, with participants’ consent. (An interviewee may request that the interviewer take handwritten notes, as opposed to a recording, though this is not feasible for focus group discussions.) All recordings and notes will be confidential and shared only among research team members. All interviews and focus group discussions will be anonymised immediately upon transcription (discussed further below). All recordings will be destroyed once transcription has been completed and checked. A separate list of participants will be held securely at each site, to allow the return of findings to participants.

### Data analysis

Quantitative data will be analysed using Stata statistical software [56]. Descriptive characteristics of study participants will be reported. WHOQOL-BREF total scores will be calculated, and we will report endline score adjusting for baseline score to determine improvement over time. The scores of self-completed and proxy-completed questionnaires will be compared graphically to assess their correlation, and the validity of proxy-completed WHOQOL-BREF will be investigated against self-completion as the gold standard. Qualitative interview and focus group transcripts will be analysed in ATLAS.ti [57] using thematic analysis, following a process of coding of themes and grouping into categories. A framework analysis approach [58, 59] will be adopted to develop a standardised coding frame that can be used across all countries to allow cross-country comparison of the results. The coding frame will be sufficiently flexible to allow addition of emerging country-specific themes during the analysis. Each SUCCEED country team will be responsible for coding their own data, led by the Country PI. Each focus group discussion or interview will be analysed by two coders. Regular meetings will bring together country teams with LSHTM team to discuss progress of coding.

All qualitative data will initially be analysed in the local language to avoid losing information and nuances specific to local language in the translation processes. However, the multi-site, cross-country nature of this study will necessitate translation of all transcripts into English. Where analysis in a local language is not possible, or for cross-country analyses of the data, analyses will be carried out in English with input from the country team members to check appropriateness of analysis and interpretation.

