## Methods

### Study design

The pilot will use a before-and-after study design without a control group to assess changes in subjective quality of life among participants with lived experience of psychosis who are offered the SUCCEED Africa intervention over a 4-month follow-up period. Nested within this study are several other components:A baseline assessment of the feasibility and acceptability of the WHO’s Quality of Life Brief Version (WHOQOL-BREF) as a measurement tool (time taken to administer, proportion of participants who complete the tool, perspectives of data collectors assessed through interviews), face validity (assessed through cognitive interviewing), and the validity of proxy (completed by a close family member) versus self-completion.An endline qualitative study using a combination of focus groups (participants with psychosis, family members) and interviews (PSW, CSW, supervisors, data collectors) to further examine the acceptability and feasibility of SUCCEED’s research tools (including WHOQOL-BREF) and processes.A process evaluation drawing on semi-structured observations and routine monitoring and evaluation (M&E) of intervention delivery, competency assessment of the two frontline providers (PSW and CSW), research administrative data (adverse events, drop-outs) and endline qualitative data (see above) to assess key process indicators and client-level (satisfaction), service-level (efficiency, safety, effectiveness, equity, patient-centredness, timeliness) and implementation (acceptability, appropriateness, feasibility) outcomes.

We followed Proctor et al.’s (2011) [35] conceptual framework for outcomes of implementation research to structure our investigation of client-level, service-level and implementation outcomes. This protocol was written in adherence to the Standard Protocol Items: Recommendations for Interventional Trials (SPIRIT) and Template for Intervention Description and Replication (TIDieR) checklists [36, 37] (see Additional File #2), approved by ethics committees and other institutional review boards in each of the five SUCCEED partner countries (see “Ethics”) and registered retrospectively on ClinicalTrials.gov (reference number 28346).

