### Outcomes

#### Primary outcome

The primary outcome for the before-and-after study is improvement in the quality of life of adults with lived experience of psychosis, assessed via WHOQOL-BREF (abbreviated World Health Organisation Quality of Life questionnaire) administered at baseline and endline. WHOQOL-BREF is a 26-item measure evaluating the individual’s perception of their health and wellbeing over the previous 2 weeks [47]. It is designed to be self-administered, though it is increasingly being administered by proxy (e.g. caregiver assessment) for situations in which participants are too unwell or the tool proves too burdensome for self-completion [48]. It covers four domains (physical, psychological, social relationships and environment), and each item is answered on a 5-point Likert scale, where 1 indicates “not at all” and 5 indicates “a large amount”. The total score across these items is then transformed onto a scale of 0–100, with higher scores indicating better quality of life [49]. While WHOQOL-BREF is widely used internationally, with over 100 culturally adapted translations to-date [50], it may not adequately capture the cultural nuances and specific experiences of participants across all four SUCCEED countries. Hence, additional methods will be used to evaluate WHOQOL-BREF’s performance as a measurement tool for the pilot in preparation for larger-scale research, as described below in Table 5.

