##### Client-level outcomes

Besides quality of life, the primary outcome describes above, the main client-level outcome under investigation is satisfaction (which can also serve as an indicator of acceptability). Questions regarding the satisfaction of participants with lived experience of psychosis and their family members are integrated into focus group discussion guides, with the aim of identifying common themes to be integrated into a structured satisfaction survey for a more systematic assessment of satisfaction as part of SUCCEED’s future research.

Service outcomes included in Proctor et al.’s (2011) framework are adapted from the Institute of Medicine’s Standards of Care and include the following: efficiency, safety, effectiveness, equity, patient-centredness and timeliness [35]. For the pilot, questions regarding all seven of these outcomes are integrated into discussion guides for focus groups and interviews. We will also use quantitative methods to investigate the following:Safety: The number and type of serious adverse events reported over the course of the study.Effectiveness: Change in WHOQOL-BREF (see above) for participants with psychosis, between baseline assessment and four-month follow-up.Equity: Number of participants with lived experience of psychosis (and family members) recruited and percentage who drop-out, disaggregated by gender, marital status, number of children, religious affiliation, ethnicity, level of education and employment status.Timeliness: Average time between recruitment and initiation of services, and average time between contacts with service providers, according to M&E data.

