### Sample size

For each of the four SUCCEED sites, we expect to recruit 10 people with lived experience of psychosis and up to 10 family members (one for each participant with lived experience of psychosis, although participation of a family member is not mandatory). We will also include the PSW, CSW and supervisor involved in delivery, as well as the data collector(s) involved in administering the WHOQOL-BREF at baseline. Across the four sites, this would yield approximately 96 participants, in total.

For the purposes of the pilot, we do not expect to recruit a representative sample of people with psychosis; rather, we will purposively select a sample of 10 people with psychosis, aiming to maximise variation across a range of sociodemographic (described below) and clinical (diagnosis) characteristics to better ensure a diverse representation. This is to aid in identifying any unforeseen barriers that may affect willingness or ability to participate in the intervention.

In determining the sample size, the need for variation is weighed against several practical considerations: (1) what the SUCCEED research team felt would be a reasonable caseload for the frontline providers involved in delivery; (2) a desirable group size for livelihoods and self-help activities; (3) a desirable group size for subsequent focus group discussions, for research purposes. We also note that this sample size is in line with those of similar studies piloting CBR for schizophrenia (“RISE” as described in Asher, et al. 2018) [26] and peer support for people with severe mental health conditions, including psychosis (“UPSIDES” as described in Puschner et al. 2019) [40] in sub-Saharan Africa. Both studies recruited 10 participants with mental health conditions; RISE recruited “dyads” with one family member for each participant with a mental health condition.

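### Endline score adjusted for baseline does not itself estimate change in a single-group study; the protocol should name the mean paired change

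*Protocol article*

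**What the plan says.** The Study design section of the protocol article describes a single group: "The pilot will use a before-and-after study design without a control group to assess changes in subjective quality of life". The Primary outcome section sets the target: "The primary outcome for the before-and-after study is improvement in the quality of life of adults with lived experience of psychosis". The score is a total on a 0–100 scale, with higher values better. The list of quantitative measures under Client-level outcomes states the quantity more precisely: "Change in WHOQOL-BREF (see above) for participants with psychosis, between baseline assessment and four-month follow-up".

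The Data analysis section gives one sentence on how this outcome will be analysed. WHOQOL-BREF totals will be calculated, and "we will report endline score adjusting for baseline score to determine improvement over time". The article mentions no paired difference, change score, time effect or other contrast of endline with baseline.

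The Sample size section gives the numbers per site: "we expect to recruit 10 people with lived experience of psychosis and up to 10 family members". There are four sites.

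**The concern.** Adjusting a follow-up score for baseline is a sound way to sharpen a comparison between groups, because the quantity of interest is then the group coefficient. Here there is no group coefficient. A regression of endline on baseline in one group returns a level and a slope, and neither is a change from baseline. The sentence thus pairs a method with a purpose that the method does not serve.

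Two things are at stake. An analyst who follows the sentence literally reports an adjusted endline level and leaves the reader to work out the change. An analyst who subtracts the baseline mean, but takes the standard error from the regression, reports the right estimate with too narrow an interval. The Discussion says the pilot is to inform two randomised trials and further process evaluations, so the change and its variability should be reported plainly and correctly.

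**Working it through.** **Inputs from the protocol article.** One group (Study design). Two time points about four months apart (Endline). 10 people with psychosis at each of 4 sites, so n = 4 × 10 = 40 (Sample size). Score range 0–100 (Primary outcome).

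**Assumptions, because the article gives no such figures.** SD 15 at both time points, varied from 10 to 20; baseline-endline correlation r = 0.6, varied from 0.3 to 0.7; mean 50 in the simulation; no drop-out.

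**The plan's own figure.** The article states no expected change, SD or precision for this outcome, so there is none to reproduce. Its total of about 96 participants is a headcount: 4 × (10 + 10 + 3 + 1) = 96, taking one data collector per site. Of these, 40 contribute to this outcome.

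**Step 1: what the adjusted mean is.** Let x be baseline, y endline, x̄ and ȳ their means, and b the fitted slope. The least-squares line passes through the two means, so the predicted endline at the mean baseline is

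(ȳ − b·x̄) + b·x̄ = ȳ.

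This is the raw endline mean, exactly and with no assumption about the data.

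**Step 2: what the slope is.** With equal SDs the slope estimates r. In simulation it averaged 0.30, 0.50 and 0.70 for r = 0.3, 0.5 and 0.7, whether the true change was 0, +5 or −5 points. It carries no information about improvement.

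**Step 3: recovering the change.** Subtracting x̄ gives ȳ − x̄, the mean paired change. The point estimate is then right. Its variance across samples is

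2·SD²·(1 − r)/n,

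whereas the regression standard error squared is

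SD²·(1 − r²)/n,

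which treats the baseline mean as fixed. The shortfall is SD²·(1 − r)²/n. At SD 15, r = 0.6, n = 40:

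- paired: 2 × 225 × 0.4/40 = 4.5, so SE 2.12 and half-width 2.02 × 2.12 ≈ 4.3 points;
- regression: 225 × 0.64/40 = 3.6, so SE 1.90 and half-width 2.02 × 1.90 ≈ 3.8 points.

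The ratio of the two standard errors is √((1 + r)/2) = √0.8 = 0.89, so the interval is about 10% too narrow.

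**Step 4: error rate.** Simulation with no true change, n = 40, SD 15, 5,000 datasets per row:

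| r | SE, regression | SE, paired | False positives, regression SE | False positives, paired |
|---|---|---|---|---|
| 0.3 | 2.24 | 2.78 | 10.7% | 4.9% |
| 0.5 | 2.04 | 2.35 | 9.0% | 5.4% |
| 0.7 | 1.69 | 1.83 | 7.0% | 5.1% |

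**Step 5: precision of the paired change.** At n = 40 the 95% half-width runs from 2.5 points (SD 10, r = 0.7) to 7.6 points (SD 20, r = 0.3). For one site of 10 at SD 15 and r = 0.6 it is 2.26 × 15 × √0.8/√10 ≈ 9.6 points, so site-level results will be descriptive only.

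**The case against.** The best defence is that one condensed sentence in an article is being read too literally. It names no regression model, coefficient, test or interval. Its stated purpose is improvement over time, and the outcome is defined elsewhere as change, so the team may simply mean endline relative to baseline. Model form is properly left to a fuller document. Both scores are collected for each person. A model of the difference on mean-centred baseline has the mean change as its intercept, so baseline adjustment and change are not incompatible. If the later trials adjust for baseline, the endline SD and the correlation are useful planning inputs, and the paired data yield both.

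Much of this stands. It limits the point to the analysis as worded and removes any claim that change is unobtainable. It does not remove the mismatch: the sentence states both a method and its purpose, and the step that connects them is absent. A later document that follows the sentence literally inherits the problem, and one that corrects it departs from the published text.

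Two stronger readings are tempting, and the article supports neither. A reader might infer that the team will test the intercept or slope and report a spurious improvement; no such test is planned. A reader might also object to listing an uncontrolled change under effectiveness. That label comes from the outcome framework the article cites, and the article openly calls the design uncontrolled and leaves the evaluation of effectiveness to future research.

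**Conclusion.** The point holds in limited form. In this one-group design, the analysis named for the primary outcome does not itself estimate the change that the protocol defines as that outcome. That part is algebra and rests on no assumed values.

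The numerical consequence is modest and conditional. It arises only if change is recovered by subtraction while the regression standard error is kept. The interval is then about 10% too narrow at r = 0.6, and the nominal 5% error rate becomes about 7% to 11% for correlations from 0.7 to 0.3. These figures assume equal SDs at both time points and complete data on 40 people; the half-widths in points also depend on the assumed SD of 15.

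This should be corrected, but it is not critical. The pilot has a purposive sample and no power calculation, and the article states no decision rule that depends on this result.

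**What to change.** In Data analysis, replace the clause on endline adjusted for baseline with:

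*The primary analysis is the mean paired change (endline minus baseline) with its 95% CI from the paired differences, overall and by site; the SD of change and the baseline-endline correlation will also be reported.*

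The cost is one sentence and no new data. The interval becomes slightly wider than one based on the regression standard error, about 4.3 against 3.8 points under the assumptions above, and that wider interval is the correct one for a mean change. The outcome list needs no change.

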#### Adherence

As this is a pilot study, fidelity of intervention delivery and adherence by participants with lived experience of psychosis and family members are important indicators of feasibility and acceptability that we seek to capture through routine M&E, semi-structured observations and reporting (described further below in “Routine monitoring and evaluation” and in Table 5)—which also offer opportunities for supervisors to identify and resolve any quality assurance issues on an ongoing basis. Participants with lived experience of psychosis are expected to receive one initial home visit (or alternative location if preferred) within 2 weeks of recruitment, followed by (at minimum):Four monthly face-to-face visits with PSW plus four monthly follow-up contacts (which may take place face-to-face or remotely)Four monthly face-to-face visits with CSW plus four monthly follow-up contacts (which may take place face-to-face or remotely)Four monthly PSW-facilitated self-help group meetings with livelihood activities

**Table 5 Tab5:** Assessment of WHOQOL-BREF embedded in pilot study

**Topic**	Timepoint		Participants			**Methods**
	**Baseline**	**Endline**	**Participants with lived experience of psychosis**	**Family members**	**Data collectors**	
Face validity	X		X	X		Cognitive interview immediately following completion of WHOQOL-BREF
Validity of completion by proxy	X		X	X		Comparison of WHOQOL-BREF completed by participant with lived experience versus family member
Acceptability and feasibility	X				X	Interview following completion of baseline for all participants
		X	X	X		Questions related to WHOQOL-BREF integrated into endline focus group discussions
		X			X	Analysis of research process data recorded by data collector (time taken to administer, proportion of participants who complete all WHOQOL-BREF questions)

Family members enrolled in the pilot will also be offered four monthly self-help group meetings with livelihood activities facilitated by the CSW.

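### The self–proxy comparison of WHOQOL-BREF names only correlation, which is blind to a systematic difference in level; agreement should be the stated target

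*Protocol article*

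**What the plan says.** The Study design section of the protocol article lists, within the baseline assessment of WHOQOL-BREF, "the validity of proxy (completed by a close family member) versus self-completion". Table 5 gives the method for this topic as "Comparison of WHOQOL-BREF completed by participant with lived experience versus family member", at baseline, without saying what kind of comparison.

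The Data analysis section is the only place that says more, in one sentence with two clauses: the self- and proxy-completed scores will be "compared graphically to assess their correlation, and the validity of proxy-completed WHOQOL-BREF will be investigated against self-completion as the gold standard".

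The first clause names a form (graphical) and a property (correlation). The second names a reference standard but no statistic. No mean paired difference, limits of agreement, intraclass correlation or concordance coefficient appears in the article, and there is no criterion for calling the proxy valid.

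On context, the Primary outcome section describes a total score transformed to 0–100. It notes that the instrument is increasingly completed by proxy in general use, "for situations in which participants are too unwell or the tool proves too burdensome for self-completion". Under Baseline, the family member's proxy assessment is collected alongside the participant's own, which may be self-administered or taken by interview. The endline measure is described as a self-assessment.

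**The concern.** If the question is whether a proxy score can be read as a self score, two things matter: whether the two rank people alike, and whether they sit at the same level on the 0–100 scale. Correlation addresses only the first. A group of relatives who all rated quality of life lower than the participants did, by a constant amount, would correlate with self-report exactly as well as unbiased relatives.

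This goes beyond an analysis detail left for later. The article names a target for the comparison, and it is the wrong one for the stated aim. An analysis that followed the sentence literally could report a high correlation under the label of validity while saying nothing about bias. Objective 2.2 in Table 1 is to assess WHOQOL-BREF as the primary outcome measure for a trial, so what is reported about proxy completion may be read by those designing later work.

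A second, smaller point concerns reach. A pair exists only where the participant has given answers. The comparison therefore informs about people able to answer, by themselves or by interview, and the wording on a gold standard does not say so.

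**Working it through.** **Number of pairs.** The Sample size section says "we expect to recruit 10 people with lived experience of psychosis and up to 10 family members" per site, and "Across the four sites, this would yield approximately 96 participants, in total". Taking one data collector per site (the article allows more than one) and adding the PSW, CSW and supervisor: 4 × (10 + 10 + 3 + 1) = 96, which reproduces the stated total. The number of self–proxy pairs is at most 4 × 10 = 40, and fewer if some participants have no enrolled relative.

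**Correlation under a shift (no assumption needed).** For any constant b, corr(X, Y − b) = corr(X, Y), because subtracting a constant changes neither the covariance nor the SDs. In one simulated set of 40 pairs, lowering every proxy score by a further 0, 10, 15 or 20 points gave:

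| Shift | Correlation | Mean difference (proxy − self) |
|---|---|---|
| 0 | 0.884 | −1.3 |
| 10 | 0.884 | −11.3 |
| 15 | 0.884 | −16.3 |
| 20 | 0.884 | −21.3 |

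**What an agreement measure would show.** The documents give no SD, correlation or bias. Assumed: SD = 15 for both raters, r from 0.6 to 0.9, bias b from 0 to 20 points (absolute size).

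Lin's concordance with equal SDs: CCC = 2·r·SD² / (2·SD² + b²). For r = 0.80 and b = 15: 2 × 0.80 × 225 / (450 + 225) = 360 / 675 = 0.53.

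| Bias (points) | r | CCC |
|---|---|---|
| 0 | 0.80 | 0.80 |
| 5 | 0.80 | 0.76 |
| 10 | 0.80 | 0.65 |
| 15 | 0.80 | 0.53 |
| 20 | 0.80 | 0.42 |

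At a 15-point bias the concordance is 0.40 for r = 0.6 and 0.60 for r = 0.9.

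The SD of the paired differences is SD·√(2(1 − r)) = 15 × √0.4 = 9.5 at r = 0.80. The 95% limits of agreement for a 15-point bias are 15 ± 1.96 × 9.5, that is −3.6 to 33.6 (signs reversed if the proxy scores lower).

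**Is it estimable at the planned size?** With 40 pairs, the 95% CI half-width for the mean difference is t(0.975; 39) × SD of differences / √40:

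- r = 0.6 (SD of differences 13.4): 4.3 points
- r = 0.8 (9.5): 3.0 points
- r = 0.9 (6.7): 2.1 points

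Under these assumptions a 10-point bias would be clearly visible with the full 40 pairs. In a single site with 10 pairs the half-width at r = 0.8 is 6.8 points, so site-specific estimates would be rough.

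**The case against.** The strongest reply is that the sentence has two clauses and should not be read as one. It does not say that validity will be judged by graphical correlation. The validity step stands separately with its method open, and a comparison against a reference standard could well include bias. The statistic may be fixed in a fuller protocol or analysis plan that is not shown. This stands in part: the absence of a named agreement statistic would be no finding by itself. What remains is that the one property the article does name is unsuited to the aim, and the open clause does not correct it.

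Second, insensitivity to a shift belongs to the correlation coefficient and not to every graph. Under the assumptions above with r = 0.80, about 85% of pairs would fall on one side of the identity line for a 10-point bias and about 94% for a 15-point bias. A scatter plot with that line, or a difference plot, would reveal this. That is correct, but the stated purpose of the graph is correlation, and neither feature is specified.

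A reader might also infer several stronger things that the article does not support:

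- That a biased proxy would pass: no threshold or accept/reject rule is stated.
- That pairs will be pooled across countries regardless of site, inflating the correlation: the article does not say how site will be handled.
- That SUCCEED plans to substitute proxies for participants who are too unwell: that passage describes general use of the instrument, and the pilot collects the proxy alongside self-completion.
- That the result decides proxy use in the later trials: the Discussion mentions two randomised trials but says nothing about proxy outcomes.
- That less well people are never represented: interview administration and guardian consent with assent mean some may contribute pairs.

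**Conclusion.** The concern holds in a limited form. For the nested aim on proxy versus self-completion, correlation is the only property the Data analysis section names, and it cannot register a systematic difference in level. That part is algebra. The size is illustrative: with an assumed SD of 15 and r = 0.80, concordance falls from 0.80 to 0.53 at a 15-point bias while the correlation stays put. Whether relatives in this study will be biased, and by how much, cannot be known from the documents.

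The primary before-and-after outcome is not affected, since endline is described as self-assessed. Any consequence for later trials is an inference. The point is nevertheless worth acting on, because a better-matched analysis exists on the same data and would be informative with up to 40 pairs.

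**What to change.** In the Data analysis section, make agreement, not correlation, the property that the self–proxy comparison assesses, and name the measures:

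1. the mean paired difference (proxy minus self) with its 95% CI;
2. a Bland-Altman plot with 95% limits of agreement;
3. an absolute-agreement ICC;
4. each accounting for site.

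Correlation may be kept as a supplement. Add a sentence stating that the conclusion applies to participants able to answer the questionnaire themselves, whether self-administered or by interview.

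The cost is slightly more analysis, a narrower claim, and an agreement figure that may look less favourable than the correlation would. No extra data collection is needed.
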